### Recruitment

Potentially eligible participants will be identified by the clinical care team at the Older People Memory Outpatient Clinic of the Clinical Hospital, Faculty of Medicine, University of São Paulo. This team will conduct cognitive and mood assessments. If the participant is willing to participate, a qualified person will provide verbal and written information about the study.

### Randomization

Participants will be randomly assigned to the VRG and EG with a 1:1 allocation ratio. A researcher not involved in the study will prepare the randomization schedule from a computer-generated list of random numbers.

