### Eligibility criteria

#### Inclusion criteria

The following will be included: 1) Older people individuals (> 60-years-old); 2) Both genders; 3) Adequate proficiency in the Portuguese language; and classified in one of the following two categories: (3) Mild NCD – at least one domain with a composite score less than or equal to −1, but without criteria for dementia; (4) Mild Major NCD with a CDR (Clinical Dementia Rating scale) <2; and (5) Agreeing to participate in the study by signing the consent form.

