### Sample size

The sample size calculation was based on a review with meta-analysis regarding the effectiveness of VR for individuals with mild cognitive impairment or dementia, which produced small to medium effect sizes using a random effects model (effect size = 0.29) from a total of 11 studies.^36^ Assuming a dropout rate of 20 %, a total sample size of 32 participants (16 per treatment group) would provide a power of 0.8 with a two-tailed α error of 0.05.

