### Data analysis

Continuous variables will be presented as mean and standard deviation, while categorical variables will be expressed as absolute frequencies (n) and percentages ( %). The distribution of the data will be assessed using the Shapiro-Wilk test. The Z-score will be used to normalize non-parametric data. Continuous data will be analyzed using the General Linear Model (GLM) for repeated measures and univariate GLM for group comparisons. The effect size and 95 % Confidence Interval will be reported along with their interpretations. The significance level will be set at α ≤ 0.05, and when applicable, clinical details related to the instruments, such as the minimum detectable change and measurement error, will also be included. Data analyses will be conducted using SPSS version 24.0.

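### Mild NCD and mild major NCD are pooled in 32 participants, but no stratification is described and the named models include neither diagnosis nor the baseline score as a covariate

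*Protocol article*

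**What the plan says.** - **Population.** Under Inclusion criteria, participants must be "classified in one of the following two categories": mild NCD, where dementia criteria are not met, or mild major NCD with a CDR below 2. No expected mix or quota is given.
- **Allocation.** The Randomization section says "Participants will be randomly assigned to the VRG and EG with a 1:1 allocation ratio", and that a researcher outside the study will "prepare the randomization schedule from a computer-generated list of random numbers". It mentions neither blocks nor strata.
- **Size.** The Sample size section plans "a total sample size of 32 participants (16 per treatment group", with 20% dropout.
- **Analysis.** The Data analysis section names a GLM for repeated measures and "univariate GLM for group comparisons". It lists no covariate or stratification factor.
- **Outcomes.** Table 3 includes cognitive and functional measures, the areas in which the two diagnoses differ by definition. Assessments are made once before and once after the intervention.

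**The concern.** In a trial this small, chance alone can give one arm noticeably more participants with mild major NCD. If that group scores lower after the intervention, or changes differently, part of any difference between the arms reflects case mix. As described, neither the allocation nor the models deal with this. Two variables that could absorb it, diagnosis and the baseline score, are collected before allocation and are not named in the analysis. Hypothesis 1 claims superiority over an active comparator, so the result rests on what may be a modest contrast.

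**Working it through.** **Inputs.** From the protocol article: 32 allocated 1:1, 20% dropout, effect size 0.29 with no metric stated, one assessment before and one after. Assumed: K = 8 to 16 of the 32 have mild major NCD; the diagnoses differ by 0.5 to 1 SD; pre-post correlation r = 0.5 to 0.8.

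**The plan's own figure.** Read as a standardised mean difference, 0.29 needs 2 × (1.960 + 0.842)² / 0.29² ≈ 187 per arm, so 32 is not reproduced. About 32 appears if 0.29 is Cohen's f for the group-by-time interaction with r = 0.5: 26 evaluable, and 26 × 1.2 = 31.2, rounded up to 32. Neither f nor r is stated. That is a separate matter; here 32 is only the number allocated.

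**Step 1: chance of a gap of at least 20 points in the share with mild major NCD.**

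- *Unrestricted list:* the numbers with and without mild major NCD in one arm are independent Binomial(K, 0.5) and Binomial(32 − K, 0.5).
- *List fixed at 16:16:* the number *a* in one arm is hypergeometric and the gap is |2a − K|/16. For even K, the smallest gap that reaches 20 points is 4/16 = 25 points.

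| K | Unrestricted | Fixed 16:16 |
|---|---|---|
| 8 | 20% | 22% |
| 10 | 26% | 25% |
| 12 | 30% | 27% |
| 16 | 24% | 29% |

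Example, K = 8 with 16:16: 2 × [C(16,2)C(16,6) + C(16,1)C(16,7) + C(16,0)C(16,8)] / C(32,8) = 2 × (960,960 + 183,040 + 12,870) / 10,518,300 = 0.220.

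For odd K with 16:16 the gap jumps from 3/16 (18.75 points) to 5/16 (31.25 points), so the 20-point cut falls between the two. At K = 9, a gap of 18.75 points or more has probability 1 − 2 × C(16,4)C(16,5)/C(32,9) = 1 − 15,899,520/28,048,800 = 0.43. A gap of 31.25 points or more has probability 3,180,320/28,048,800 = 0.11. The figure of 20-30% sits between these.

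**Step 2: what a gap does.** The shift in a post-score contrast without covariates is gap × difference between diagnoses.

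- 0.25 × 0.5 SD = 0.125 SD
- 0.25 × 1 SD = 0.25 SD

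In the repeated-measures model the group-by-time contrast removes baseline level. The same formula then applies only to the difference in *change* between diagnoses, for which the documents give no figure. If change does not differ by diagnosis, the shift is zero.

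**Step 3: what baseline adjustment gains.** With equal pre and post variances, the change contrast has variance proportional to 2(1 − r) and the baseline-adjusted contrast to 1 − r². The ratio is (1 + r)/2.

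- r = 0.5: 0.75, a 25% reduction
- r = 0.8: 0.90, a 10% reduction

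These are large-sample ratios. With q covariates and N analysed, adjusting for chance covariate imbalance multiplies the variance by about 1 + q/(N − q − 3). For N = 26 (32 × 0.8 = 25.6) and q = 2 this is 1 + 2/21 = 1.095. If diagnosis predicted nothing beyond the baseline score, the net ratios would be 0.75 × 1.095 = 0.82 and 0.90 × 1.095 = 0.99. Any prediction by diagnosis improves on that.

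**The case against.** The strongest reply is that this is an absence in a condensed article. Random-number lists are also how blocked, stratified or fixed 16:16 schedules are made, and a GLM can take covariates. Blocks, strata or covariates may be set out in a fuller document. This stands in part: the text does not say that the list is unrestricted or that the models are unadjusted. It does name the list and the models, however, and neither handles diagnosis as written. The result in Step 1 also does not depend on how the list is restricted, unless it is stratified by diagnosis.

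Four stronger readings are tempting, and the documents do not support them.

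- **That the arms will be unequal in size.** This needs an unrestricted list, which is not stated; 1:1 with 16 per group also fits a fixed list. Even a 20:12 split keeps 4 × 20 × 12 / 32² = 94% efficiency.
- **That imbalance could be as large as the planned effect.** Under the 1 SD assumption, matching 0.29 takes a 29-point gap. For even K that occurs in about 4-12% of trials under either list; for odd K with 16:16 it is 11% at K = 9 and stays below one in six up to K = 15. The metric of 0.29 is also unstated. As Cohen's f it corresponds to d = 0.58, and 0.25 is then 43% of it.
- **That diagnosis is the strongest prognostic factor.** The article shows that the categories differ in severity, not how well they predict response to training.
- **That chance imbalance biases the trial.** Over repeated randomisations the type I error is preserved.

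The article also describes the project, under Dissemination policies, as preliminary to a definitive trial. That lowers the stakes, but a preliminary estimate still benefits from precision.

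**Conclusion.** The point holds as one of precision and interpretability. With 8 to 16 participants with mild major NCD, a gap of 20 points or more in that share arises in about 20-30% of trials. Under a 16:16 list with an odd count, the exact figure depends on which side of 20 points the possible gaps fall. A 25-point gap moves a post-score contrast without covariates by 0.125-0.25 SD. It moves the pre/post contrast only if change differs by diagnosis. Baseline adjustment lowers the variance by about 10-25% relative to the change contrast, less a small-sample cost that nearly cancels the gain at r = 0.8 if diagnosis adds nothing. The diagnostic mix, the difference between diagnoses and the correlation are all assumptions, because the article gives none of them. It is worth changing because it is cheap, not because the design is invalid.

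**What to change.** Before any unblinded analysis, prespecify for each continuous outcome in Table 3 a GLM of the post-intervention score on three terms: arm, the baseline score of the same measure, and diagnosis as classified at entry (mild NCD or mild major NCD). Make the arm coefficient with its 95% confidence interval the between-group result. State in one sentence whether the randomisation list is restricted or stratified; if a fuller document already covers these items, cite it.

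The cost is one degree of freedom per added term (residual 26 − 4 = 22 rather than 24 with 26 analysed) and a short amendment. No new data are needed.

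Stratified blocks for participants not yet allocated are optional. About half are already recruited, so blocks would not undo any imbalance so far, and small blocks are easier to predict where facilitators are unblinded. The model terms cover everyone analysed, including those already allocated.

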### Blinding

It will not be possible to blind the participants from the test and the intervention facilitator. All outcomes will be assessed by a researcher who is blinded to group allocation. Participants will be asked not to disclose their allocation to the physiotherapist conducting the assessments. This team will conduct cognitive and mood assessments. If the participant is willing to participate, a qualified person will provide verbal and written information about the study.

### Data collection

Demographic data will be obtained through electronic forms, including a question regarding previous COVID-19 infection as a demographic variable to be considered. In real-time, trained professionals will conduct questionnaires and assessments, entering the results directly into the Research Electronic Data Capture (REDCap).

Demographic data will be obtained through electronic forms. In real-time, trained professionals will conduct questionnaires and assessments and will enter the results directly into the Research Electronic Data Capture (REDCap).

### Data management and monitoring

All research data will be collected directly in REDCap, at the FM-USP instance, and stored on a server in the USP cloud (MySQL), with automatic internal backups and daily backups on the institutional Google Drive, in addition to firewall protection.

### Data analysis

Continuous variables will be presented as mean and standard deviation, while categorical variables will be expressed as absolute frequencies (n) and percentages ( %). The distribution of the data will be assessed using the Shapiro-Wilk test. The Z-score will be used to normalize non-parametric data. Continuous data will be analyzed using the General Linear Model (GLM) for repeated measures and univariate GLM for group comparisons. The effect size and 95 % Confidence Interval will be reported along with their interpretations. The significance level will be set at α ≤ 0.05, and when applicable, clinical details related to the instruments, such as the minimum detectable change and measurement error, will also be included. Data analyses will be conducted using SPSS version 24.0.

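### The Z-score rule for non-normal outcomes cannot change a distribution's shape and, depending on how it is computed, can distort the pre-post comparison

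*Protocol article*

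**What the plan says.** The Data analysis section of the protocol article sets out a sequence.

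- Check: "The distribution of the data will be assessed using the Shapiro-Wilk test".
- Remedy: "The Z-score will be used to normalize non-parametric data".
- Model: "Continuous data will be analyzed using the General Linear Model (GLM) for repeated measures and univariate GLM for group comparisons".
- Interpretation, where applicable: "clinical details related to the instruments, such as the minimum detectable change and measurement error, will also be included".

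Descriptive summaries are covered separately: "Continuous variables will be presented as mean and standard deviation". The section names no transformation that changes shape, no rank-based test, and no bootstrap or robust method. It does not say whether the Z-score uses a pooled mean and SD, those of each time point, those of each group, or external norms.

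**The concern.** The sentence is a positive rule, not a detail left open, and on its ordinary meaning it does not do what it is there to do. Subtracting a mean and dividing by an SD is a straight-line transformation. Skew, heavy tails and pile-up at a floor or ceiling all survive it.

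Two further consequences depend on how the rule is carried out. The design has one assessment before and one after the intervention, and the first hypothesis is a difference between groups in improvement. Some ways of computing a Z-score remove the very means that carry this information. In addition, model estimates on a Z scale are in SD units, while minimum detectable change and measurement error are in instrument units, so the two cannot be set side by side without converting back.

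**Working it through.** There is no stated figure to reproduce; the point is algebraic, with a numerical check.

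**Inputs.** From the Sample size section: 32 participants, 16 per group, 20% dropout, which leaves 32 × 0.8 = 25.6, or about 13 per arm. From the design: two groups and two time points. Assumed, because the document gives no outcome distributions: lognormal data with log-scale SD 0.8, simulated for 16 per group at two time points with no true effect.

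**Step 1: shape.** Let z = (x − m)/s with s > 0. Skewness is the mean of ((x − m)/s)³, and excess kurtosis is the mean of ((x − m)/s)⁴ minus 3. Both are already computed from standardised values, so they do not move. Shapiro-Wilk W is a ratio of two quantities that each scale with 1/s² and ignore m, so it does not move either.

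| Simulated data, n = 32 | Raw | Z-scored |
|---|---|---|
| Time 1: Shapiro-Wilk W | 0.7412 | 0.7412 |
| Time 1: Shapiro-Wilk p | 3.8 × 10⁻⁶ | 3.8 × 10⁻⁶ |
| Time 1: skewness | 2.694 | 2.694 |
| Time 1: excess kurtosis | 9.21 | 9.21 |
| Time 1: group comparison p | 0.4988 | 0.4988 |
| Time 2: Shapiro-Wilk W | 0.7292 | 0.7292 |
| Time 2: skewness | 2.765 | 2.765 |
| Time 2: group comparison p | 0.9605 | 0.9605 |

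**Step 2: effect on the repeated-measures model.** With two time points, the group-by-time test is the two-sample test of the change scores. Write V and E for the virtual reality and exercise group means, with subscript 1 for before and 2 for after. The raw interaction is (V₂ − V₁) − (E₂ − E₁).

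- *One common m and s:* the interaction becomes [(V₂ − V₁) − (E₂ − E₁)]/s. Its standard error is also divided by s, so F is unchanged.
- *Separate m₁, s₁ and m₂, s₂ at each time point:* every time point now averages zero, so the mean change over all participants is zero by construction. The interaction becomes (V₂ − E₂)/s₂ − (V₁ − E₁)/s₁, which is a different quantity whenever s₁ and s₂ differ.
- *Separate m and s within each group and time point:* all four cell means are zero, so the interaction is zero by construction.

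| Z-score computed | Group-by-time F | p | p for overall change |
|---|---|---|---|
| Not applied (raw) | 0.2806 | 0.600 | 0.576 |
| Common mean and SD | 0.2806 | 0.600 | 0.576 |
| Per time point | 0.2667 | 0.609 | 1.000 |
| Per group and time point | about 0 | 1.000 | not computed |

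The per-time-point shift is small in this sample. In another simulated skewed sample the interaction p moved from 0.63 to 0.88, so its size varies with the data.

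**Step 3: does leaving the skew in place invalidate the tests?** Null simulations used 40,000 runs per case and an assumed latent pre-post correlation of 0.6, with t-tests on the post score and on the change score. The outcomes were lognormal, exponential, or rounded scores piled at a floor of 0. Across the simulations, Type I error at a nominal 5% was about 3.9% to 5.2% with 13 or 16 per arm. An uneven 15/11 split gave 4.1% to 4.9%.

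**Step 4: what an effective remedy could gain.** With 13 per arm and an assumed lognormal outcome, replacing the raw-score test by one on rank-based normal scores raised power from about 0.56 to about 0.68. A post-score shift of one SD on the log scale gives a gain of this size (0.55 to 0.67 on repeating it). That is a large assumed effect, and the gain is illustrative only.

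**The case against.** The strongest reply is that a step that changes nothing does no harm: with a common mean and SD, the analysis is exactly where it would be without the sentence. A reader might infer from the failed normality check that the p-values would be invalid. The documents do not support that. They give no outcome distributions, and the simulations in step 3 show no meaningful inflation, with slight conservatism under strong skew. This stands, within its limits: it assumes both arms share a shape under the null, and interval coverage under a real effect was not examined.

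Other tempting readings also go too far.

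- *That GLM p-values are always identical after Z-scoring.* This holds only with one common mean and SD, which the section does not specify.
- *That raw units are lost.* Under a common SD, multiplying back restores them. Descriptive means and SDs may stay in raw units, and minimum detectable change is promised only where applicable. What remains is that model estimates need converting.
- *That the check is wrongly aimed at raw data and not at residuals.* The article speaks only of the distribution of the data. Which quantity is tested is detail that a full analysis plan may settle.
- *That a report would declare the problem solved, or that particular questionnaires will pile up at one end.* The article says neither.

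Finally, rank-based normal scores may have been meant, and those do change shape. The text does not say so, and the sentence would still need rewriting.

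**Conclusion.** The rule is wrong as written. On the ordinary meaning of a Z-score, the only remedy given for non-normal data corrects nothing; this is exact and does not rest on the simulation.

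The size of the harm depends on implementation. With a common mean and SD it is nil for the test itself, apart from whatever power is forgone by having no effective remedy for skewed outcomes. With scoring per time point, the overall change is forced to zero and the interaction is altered. With scoring per group and time point, the effect under test disappears. The article does not say which would be used, so the distortion is possible, not established.

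The power figures rest on an assumed lognormal outcome and effect. Inflated Type I error is not shown. This should be fixed, but it does not by itself invalidate the trial's analysis.

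**What to change.** Delete the Z-score sentence. Run the GLM on every continuous outcome in its instrument units, so that estimates can be read directly against minimum detectable change and measurement error. Where the distribution is clearly non-normal, add a prespecified sensitivity analysis of the group difference, either on rank-based inverse-normal scores or by permutation. If rank-based normal scores are what the sentence meant, name the method and say how ranks are formed across groups and time points.

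The cost is one changed sentence and a little extra analysis code. The drawback is that a rank-based result is not in instrument units, so it should support the raw-scale estimate and not replace it. The article reports about half of participants recruited, so if the data have not yet been analysed, the change can still be fixed beforehand.

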### Hypotheses

1.VR interventions will significantly improve postural control, gait, functionality, cognition, and mood more than the motor-cognitive integrated intervention.2.The authors hypothesize that participants undergoing VR interventions will improve their performance in the games.3.The authors expect that commercial VR games will be acceptable to older adults with mild NCD or mild major NCD. Although this population may not be familiar with this technology, commercial games were developed for entertainment in an attractive and motivating virtual environment and were easy to use.

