### Study design

The study will be a randomized, controlled, and blinded clinical trial. Participants will be divided into two groups: the VR group (VRG) and the exercise group (EG). The study assessments will be conducted before and after the intervention.

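### Two overlapping analyses are named for each continuous outcome and neither is said to decide; one baseline-adjusted ANCOVA would settle this and usually gain precision at almost no cost

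*Protocol article*

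**What the plan says.** The Data analysis section gives the inferential plan for continuous outcomes in one sentence: "Continuous data will be analyzed using the General Linear Model (GLM) for repeated measures and univariate GLM for group comparisons". It does not say which term of the repeated-measures model is the test, whether the univariate model takes post-intervention scores or changes, or whether any covariate enters.

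Four other places bear on the choice:

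- Study design fixes two time points: "The study assessments will be conducted before and after the intervention".
- Hypothesis 1 is a between-group claim: "VR interventions will significantly improve postural control, gait, functionality, cognition, and mood more than the motor-cognitive integrated intervention".
- Inclusion criteria admit two severity classes, mild NCD ("at least one domain with a composite score less than or equal to" −1) and mild major NCD.
- Randomization describes 1:1 allocation "from a computer-generated list of random numbers" and mentions no stratification by diagnosis.

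**The concern.** A repeated-measures model with two groups and two visits produces three tests:

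- **Time** compares after with before, pooled over arms. It is not a treatment comparison.
- **Group** averages the baseline visit with the post visit. Baseline carries no treatment effect, so a true post-treatment difference is halved.
- **Group-by-time** is the difference in mean change, identical to a two-sample t-test on change scores.

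Only the third addresses Hypothesis 1, and the plan does not single it out. The univariate group comparison is then a second between-group answer for the same outcome. As written it could be unadjusted, adjusted for baseline, or based on change.

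Three things are at stake. Two between-group tests per outcome, with no rule for choosing, give two chances of a false positive. Precision may be lost in a small trial. And because the deciding term is not named, a time effect or a within-arm change could later be presented as evidence of effect.

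**Working it through.** **Inputs.** From the Sample size section: "a total sample size of 32 participants (16 per treatment group"), 20% dropout, and "would provide a power of 0.8 with a two-tailed α error of 0.05". Completers: 32 × 0.8 = 25.6, taken as 26 (13 per arm). The correlation r between baseline and post scores is not in the documents; 0.3 to 0.9 is assumed, with equal SD at both visits.

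**Step 1: the plan's own figure.** The section gives "effect size = 0.29) from a total of 11 studies" without saying which effect-size metric is meant. Read as Cohen's f for the group-by-time interaction with r = 0.5, the noncentrality is f² × N × 2/(1−r) = 0.0841 × 26 × 2/0.5 = 8.75. This gives power 0.81 at N = 26. Dropout inflation gives 26 × 1.2 = 31.2, rounded up to 32, or 26/0.8 = 32.5, rounded up to 33. So 32 is reproduced. Read as a standardised mean difference, 0.29 needs 187 per arm, 374 in total and 468 with dropout. Of the readings tried, only the interaction reading reproduces 32.

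**Step 2: variance of the group contrast**, in units of the outcome variance (times 2/n). Post-only: 1. Change score, which equals the interaction: 2(1−r). ANCOVA: 1−r². Hence ANCOVA/change = (1−r²)/[2(1−r)] = (1+r)/2, and ANCOVA/post-only = 1−r².

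| r (assumed) | Post-only | Change | ANCOVA | ANCOVA/change | ANCOVA/post-only |
|---|---|---|---|---|---|
| 0.3 | 1 | 1.4 | 0.91 | 0.65 | 0.91 |
| 0.5 | 1 | 1.0 | 0.75 | 0.75 | 0.75 |
| 0.7 | 1 | 0.6 | 0.51 | 0.85 | 0.51 |
| 0.8 | 1 | 0.4 | 0.36 | 0.90 | 0.36 |
| 0.9 | 1 | 0.2 | 0.19 | 0.95 | 0.19 |

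The post-only test is less precise than the interaction only when r exceeds 0.5. The two are equal at 0.5 and the order reverses below it.

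**Step 3: small-sample correction.** These ratios treat the covariate slopes as known. Estimating p slopes from N completers multiplies the ANCOVA variance on average by 1 + p/(N−p−3). For baseline alone this is 1 + 1/22 = 1.045. For baseline plus a diagnosis term that explains nothing it is 1 + 2/21 = 1.095. Against the interaction, the model with both covariates then has 0.75 × 1.095 = 0.82 at r = 0.5, 0.85 × 1.095 = 0.93 at r = 0.7, and 0.95 × 1.095 = 1.04 at r = 0.9. A simulation with 13 per arm agreed (0.82, 0.93–0.94, 1.04). With baseline alone the ratio at r = 0.9 is 0.95 × 1.045 = 0.99.

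**Step 4: power with 26 completers.** Under the reading that reproduces 32 (f = 0.29, r = 0.5), the interaction has power 0.81. ANCOVA with baseline and a non-informative diagnosis term has 0.90 by the simple variance formula, or 0.87 by simulation with the slopes estimated. If 0.29 is a standardised mean difference, the simple formula moves power only from 0.11 to 0.13 at r = 0.5, and from 0.20 to 0.22 at r = 0.8.

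**Step 5: false positives.** Simulation: 20,000 runs, 13 per arm, no treatment effect, the same gain in both arms.

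| r | Common gain (SD) | Time | Change within VR arm | Interaction | ANCOVA | Interaction or post-only |
|---|---|---|---|---|---|---|
| 0.5 | 0.3 | 31.9% | 17.4% | 5.1% | 5.2% | 9.3% |
| 0.5 | 0.5 | 69.0% | 38.9% | 4.9% | 5.0% | 8.8% |
| 0.7 | 0.3 | 48.0% | 24.9% | 5.1% | 5.0% | 9.8% |
| 0.7 | 0.5 | 88.4% | 56.5% | 5.2% | 5.1% | 9.6% |

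The interaction and ANCOVA both hold 5%. The time and within-arm tests respond to the common gain. Accepting either between-group test nearly doubles the error rate.

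**The case against.** The repeated-measures model is not an error. Its interaction is an unbiased between-group test in a randomised trial, and the stated sample size fits it. In SPSS, which the plan names, a univariate GLM is also the procedure that fits ANCOVA, so the sentence is compatible with baseline adjustment. A condensed article may leave the covariate list to a fuller document. All of this stands. What remains is that the text commits to two analyses of the same outcomes and ties neither to Hypothesis 1.

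A reader might infer three stronger points that the documents do not support.

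- **That ANCOVA is needed to stop practice gains and regression to the mean from passing as treatment effects.** On average these are common to both randomised arms, and the interaction already removes them (Step 5). They mislead only through a time or within-arm test, which the plan leaves open but does not name as decisive. Selection below −1 SD could produce a within-arm shift of 0.15 to 0.46 SD at assumed reliabilities of 0.9 to 0.7. That shift cannot be set against the planning value of 0.29: it cancels between arms, and it concerns only the domain on which mild NCD participants were selected.
- **That the plan wastes about half its information.** The ratio 0.51 at r = 0.7 applies only if the univariate model is an unadjusted post-score comparison, which the text permits but does not state.
- **That diagnosis imbalance biases the result.** Chance imbalance is already covered by the test's error rate. With an assumed 16/16 split of diagnoses, a gap of at least 25 percentage points arises in 28.9% of allocations with 16 per arm, or about 22% with coin-flip allocation. The split is not in the documents.

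**Conclusion.** The point holds as a low-cost improvement, not as the correction of an invalid method. The plan should name one between-group contrast per continuous outcome, and baseline-adjusted ANCOVA is the better candidate. Against the interaction it removes 25% of the variance at r = 0.5, 15% at 0.7 and 5% at 0.9. With 26 completers and both covariates estimated, these become about 18%, 7% and a loss of about 4% if diagnosis explains nothing. The size therefore rests on an assumed r. The gain from the diagnosis term cannot be computed from the documents; it is reasonable because two severity classes are pooled and no stratification is mentioned. The 9–10% false-positive rate assumes that the univariate comparison is unadjusted and that either test may be counted as success. ANCOVA does not rescue the sample size if 0.29 was meant as a standardised mean difference.

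**What to change.** Replace the sentence on continuous data with wording such as:

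> For each continuous outcome, the post-intervention score will be analysed by ANCOVA with allocated group, the baseline value of that outcome and diagnostic category (mild NCD or mild major NCD). The adjusted group difference with its 95% CI is the only test of Hypothesis 1 for that outcome. Within-group change will be reported descriptively.

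The cost is plan wording and two degrees of freedom: with 26 completers, 22 error degrees of freedom instead of 24. Baseline scores and diagnostic category are already obtained at entry. The article reports about half the participants recruited, so the choice can still be fixed before outcome data are examined by group.
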